**Primary outcomes**																													
	**Heavy episodic drinking^c^**																												
		TLFB^d,e^ [48,49]					✓									✓			✓			✓			✓			✓	
		AUDIT-C^f,e^ [50]					✓									✓			✓			✓			✓			✓	
	Substance use^g^ (CRAFFT^h^ [24,44] on eligibility and TLFB all other times)			✓			✓									✓			✓			✓			✓			✓	
	**Negative consequences**																												
		Negative consequences of alcohol and cannabis use scales^e^ [51]					✓												✓			✓			✓			✓	
		PEI^i^ Personal Consequences Scale^e^ [52,53]					✓												✓			✓			✓			✓	
		NCANDA^j^ study^e^ [54]					✓												✓			✓			✓			✓	
**Secondary outcome**																													
	**Riding and driving risk frequency**																												
		National College Alcohol Study^e^ [55]					✓												✓			✓			✓			✓	
		Young Adult Driving Questionnaire^e^ [56]					✓												✓			✓			✓			✓	
		Adapted from previous cSBI^k^ studies [22,54]					✓												✓			✓			✓			✓	
**Other measures**																													
	**Hypothesized mediators**																												
		Readiness to reduce or stop use (readiness ruler [47] used in previous cSBI study [22])					✓						✓																
		Perceived risk of harm (National Monitoring the Future Survey^e^ [37])					✓						✓						✓			✓			✓			✓	
		Refusal self-efficacy (DRSEQ-SRA^l,e^ [57])					✓						✓						✓			✓			✓			✓	
		Receipt of health services for substance use (adapted from previous cSBI study [22])																	✓			✓			✓			✓	
	**Control variables**																												
		**Substance use severity profile**																											
			CRAFFT	✓					✓																				
			TLFB			✓									✓			✓			✓			✓			✓		
			ASSIST^m,e^ [58]			✓												✓			✓			✓			✓		
		Peer substance use (PEI)					✓												✓			✓			✓			✓	
		Family substance use (PEI)					✓															✓						✓	
		**Patient-clinician relationship**																											
			Number of previous visits with clinician									✓																	
			Youth Connectedness to Provider Scale [8,31]									✓																	
	**Process measures**																												
		Intervention duration (new)								✓																			
		Visit format (new)											✓																
		Protocol adherence and visit quality (adapted from previous cSBI studies [8,31])											✓																
		*Contract for Life* [43] discussion with caregivers (adapted from previous cSBI study [35])																	✓										
	**Validation of modified HONC^n^**																												
		**Nicotine use disorder risk**																											
			HONC^e^ [45,59]						✓																				
			PROMIS-E^o,e^ [60]			✓																							
	**Other exploratory variables**																												
		**Quality of life and overall health**																											
			CHU9D^p^ [61]			✓												✓			✓			✓			✓		
			PATH^q^ Study [62]			✓												✓			✓			✓			✓		
			YRBS^r,e^ [63]			✓												✓			✓			✓			✓		
		Sexual and gender minority status (YRBS and others [64-66])		✓															✓			✓			✓			✓	
		**Social determinants of health**																											
			MSPSS^s^ [67]			✓												✓			✓			✓			✓		
			YRBS			✓												✓			✓			✓			✓		

^a^CRAFFT-IS: CRAFFT (Car, Relax, Alone, Forget, Family/Friends, Trouble) Interactive System (collected before the well visit among intervention arm patients only).

^b^Monthly surveys 1, 2, 4, 5, 7, 8, 10, and 11 are brief in length; monthly surveys 3, 6, 9, and 12 are extended in length.

^c^Defined by the National Institute on Alcohol Abuse and Alcoholism Alcohol Screening and Brief Intervention for Youth Guide [68].

^d^TLFB: timeline followback.

^e^Modified or adapted for purposes of this study.

^f^AUDIT-C: Alcohol Use Disorders Identification Test–Concise.

^g^Includes alcohol, nicotine, tobacco, marijuana, inhalants, misused prescription medication, and other drugs (synthetic marijuana, stimulants, opioids, and hallucinogens).

^h^CRAFFT: Car, Relax, Alone, Forget, Family/Friends, Trouble.

^i^PEI: Personal Experience Inventory.

^j^NCANDA: National Consortium on Alcohol and Neurodevelopment in Adolescence.

^k^cSBI: computer-facilitated screening and brief intervention.

^l^DRSEQ-SRA: Drinking Refusal Self-Efficacy Questionnaire–Shortened Revised Adolescent version.

^m^ASSIST: Alcohol, Smoking and Substance Involvement Screening Test.

^n^HONC: Hooked on Nicotine Checklist.

^o^PROMIS-E: Patient-Reported Outcomes Measurement Information System Nicotine Dependence Item Bank for Electronic Cigarettes.

^p^CHU9D: Child Health Utility–9 Dimensions.

^q^PATH: Population Assessment of Tobacco and Health.

^r^YRBS: Youth Risk Behavior Survey.

^s^MSPSS: Multidimensional Scale of Perceived Social Support.

#### Other Measures

We will explore potential intervention effect moderation by age group, sexual and gender identity and social determinants of health that enhance substance use risk for sexual and gender minority youth, baseline severity of substance use involvement, peer and family substance use, and patient-clinician relationship (number of prior visits the patient had with this clinician and perceived connectedness to their clinician).

We will also examine intervention implementation measures, including the time required to deliver the various CRAFFT-IS components and patient-reported receipt and quality of substance use counseling during their visit. Time information will be collected through computerized capture of patient clickstream times and clinician counseling start and stop times, as well as clinician report of average substance use–related counseling time and overall visit length on the clinician debriefing questionnaire completed at the end of patient recruitment at a practice. Adolescents complete an immediate postvisit questionnaire that includes items on the health topics discussed during the visit, ratings of counseling quality and the degree to which it reflected an MI-based counseling style, and whether they received the *Contract for Life*.

To assess the validity of the modified HONC for identifying risk for nicotine use disorder in adolescents, we will compare it to the 4-item Patient-Reported Outcomes Measurement Information System Nicotine Dependence Item Bank for Electronic Cigarettes (PROMIS-E) [60] administered in the previsit assessment. While the CRAFFT screening items are well validated [24], the modified HONC, which now includes nicotine vaping and is included in the CRAFFT-IS previsit screening for adolescents seeing intervention clinicians, needs validation.

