#### Previsit Screening

To complete the previsit self-administered substance use screening, adolescents will log in to a secure website via their smartphone (before or at visit) or a tablet computer (at visit only) and complete the CRAFFT 2.1+N, which assesses past 12-month substance use frequency, substance-related riding and driving, and signs of problematic use (eg, uses when alone) [44]. At a cut point of ≥2 *yes* answers, the CRAFFT is highly sensitive (91%) and specific (90%) for detecting SUD in adolescents [23]. The CRAFFT 2.1+N includes an item on past 12-month days of nicotine vaping and tobacco use and, if yes, an item on past 30-day use. Endorsement of past 30-day nicotine vaping or tobacco use is followed by the Hooked on Nicotine Checklist (HONC), a well-validated 10-item screen for detecting loss of autonomy over nicotine use in adolescents [45]. This study will use a modified HONC that incorporates nicotine vaping.

After completing the substance use screen, adolescents will be asked to choose up to 3 personal values from a prespecified list of 14 values (eg, creativity, family, honesty, and wealth), with the option to write in their own. The selected values are presented in the clinician report to support clinician-patient rapport building and patient-centered MI-based counseling.

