##### Adolescents

All adolescent participants are assigned a unique numeric identifier at the time of recruitment for use in data collection, storage, and linkage throughout their study participation. Once assented, participants indicate their contact preferences. Adolescents who agree to have their data shared with the NIAAA_DA_ are assigned a Global Unique Identifier using their first, middle, and last names; sex assigned at birth; and date and city of birth. Global Unique Identifiers are numeric codes that allow participant data to be submitted to the NIAAA_DA_ without any personally identifiable information. All participants self-administer the confidential electronic previsit survey (approximately 20 min; refer to Table 2 for details on all surveys), and participants seeing an intervention clinician complete the screening and psychoeducational components of the CRAFFT-IS (5 min) before seeing their clinician. After their visit, all participants complete the immediate postvisit survey (approximately 10 min), and then, through the 12-month follow-up period, brief monthly surveys about their past 30-day substance use and longer surveys at 3, 6, 9, and 12 months (approximately 15 min each). Participants may choose to skip questions or entire surveys and still remain in the study.

All surveys can be completed electronically on smartphones and desktop or tablet computers through a link sent by SMS text message or email to participants’ personal mobile phone numbers or email addresses, as preferred. Electronic surveys are protected by a password set by the adolescent. Adolescents can also complete a survey by mobile phone with a study RA. If the adolescent does not complete a survey after electronic reminders, a study RA will call the adolescent to encourage survey completion.

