#### Data Analysis Plan

Analysts will be blinded to treatment arm. We will evaluate randomization success and level of attrition bias by comparing baseline characteristics of adolescents by treatment arm and by those retained versus those lost to follow-up (ie, adolescent participants who stop completing study surveys during the 12 months after their well visit). Baseline variables meeting a *P* value of <.20 in randomized group comparisons will be entered as control variables in multivariable modeling of the intervention effect to yield adjusted estimates of effect. We will compare rates of counseling receipt and patient ratings of their visit between groups. We will also generate variables related to intervention *dose* (eg, receipt of clinician counseling and receipt of *Contract for Life*) for use in sensitivity analyses.

To assess intervention effects on our primary and secondary outcome measures (past 90-day HED and any past 90-day riding or driving risk) at each of the 3-, 6-, 9-, and 12-month follow-up time points, we will use multiple logistic regression modeling with generalized estimating equations to compute adjusted relative risk ratios (CRAFFT-IS vs UC). Generalized estimating equations account for clustering of participants within practice and clinician. Furthermore, we will explore intervention effects on the number of days of drinking and of HED and on the number of times participants experienced alcohol-related negative consequences from baseline to each follow-up time point. As these variables are likely to have distributions that are highly skewed and overdispersed, we will specify a negative binomial distribution and log link in these regression models. We will also conduct longitudinal data analysis using mixed effects modeling to compare group outcomes trajectories through the entire 12-month follow-up period. We plan to explore intervention effect mediation by applying the product of coefficients test for mediation [71,72] and potential effect moderation by future-determined variables by testing the significance of interaction terms in regression models.

All intervention effect analyses will use intent-to-treat groups. We will transform continuous variables with skewed data and collapse categories as needed to preserve adequate cell sizes. To handle missing data, we will use multiple imputation based on regression modeling and compare the results of analyses using the imputed data set versus the original data set [73].

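### Perceived connectedness to the clinician is named as an exploratory moderator but is measured only after the intervention visit, so an arm-by-connectedness test would not describe modification by a baseline characteristic

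*Protocol article*

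**What the plan says.** The Other Measures section says that moderation will be explored by several characteristics, including the "patient-clinician relationship (number of prior visits the patient had with this clinician and perceived connectedness to their clinician". The Data Analysis Plan tests moderation by "testing the significance of interaction terms in regression models" and leaves the choice of moderators to be settled later. The Objectives section classes moderator analyses as exploratory.

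In Table 2 the instrument is the "Youth Connectedness to Provider Scale [8,31"]. It sits, with number of previous visits, in a patient-clinician relationship block under the heading "Control variables", and its only tick is in the postvisit column. The Data Collection section gives the order of events: "All participants self-administer the confidential electronic previsit survey (approximately 20 min; refer to Table 2 for details on all surveys"), then the visit, then "After their visit, all participants complete the immediate postvisit survey (approximately 10 min").

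The intervention works partly through the relationship. Rapport building is step 1 of the counseling protocol in Table 1 for all three risk profiles. Of the personal values that patients choose before the visit, Previsit Screening says: "The selected values are presented in the clinician report to support clinician-patient rapport building and patient-centered MI-based counseling".

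The covariate rule in the Data Analysis Plan is: "Baseline variables meeting a *P* value of <.20 in randomized group comparisons will be entered as control variables in multivariable modeling of the intervention effect".

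**The concern.** A moderator analysis asks whether the effect differs between kinds of patient who could be told apart before treatment. That requires a value which the arm cannot have changed. Connectedness recorded after the visit does not meet this condition. In the intervention arm, patients who score high may include some who became connected through the counseling. In the control arm, patients who score high reached that level under usual care. At the same score the two arms may therefore hold different kinds of patient, and the contrast within that level is no longer protected by randomization.

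At stake is the reading of one exploratory result. A finding that CRAFFT-IS works better, or worse, for adolescents with a strong clinician relationship could arise from how the visit sorted patients on the score. The control-variable label adds a second risk: an analyst working from Table 2 alone might adjust for the score, although the covariate rule points the other way.

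**Working it through.** No stated sample size, power or error rate depends on this point, so there is no figure to reproduce. The check compares parts of the document.

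**1. Timing.** The column can be confirmed by counting tab positions after the label in Table 2 rows at the same indent.

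| Row | Column | Basis for column | Tabs after label |
|---|---|---|---|
| PROMIS-E | Previsit | Other Measures text | 3 |
| HONC | CRAFFT-IS | Other Measures text | 6 |
| Connectedness scale | to be found | | 9 |
| TLFB, second tick | Monthly | order of column headings | 12 |

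Columns step by 3. The heading between CRAFFT-IS and monthly is the postvisit survey, so connectedness is postvisit. The row has no other tick.

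**2. Can arm change the score?** The survey follows the visit at which counseling is delivered. Rapport is an explicit counseling step, and the values items exist partly to support it. The text supports saying that the score may be affected by arm. It does not say by how much.

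**3. Comparison with similar variables in Table 2.** Readiness, perceived risk and refusal self-efficacy can also move at the visit. They are collected both previsit and postvisit and are labeled mediators. Peer and family substance use, named as moderators beside connectedness, have previsit values. Connectedness has the moderator role without a previsit value.

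**4. Number of previous visits.** This item is also asked postvisit, but it is a historical fact that the visit should not alter. The problem is specific to the connectedness scale.

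**5. Control role.** Table 2 calls the scale a control variable, while the covariate rule admits baseline variables only. A postvisit score is not one, so under a literal reading it does not enter the adjusted model.

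**6. Why the label still needs correcting.** Suppose an analyst followed the label and put the score through the P<.20 screen. This is an illustration: the size of the shift is assumed, and the ICC of 0.008 is the document's value for HED, not for connectedness.

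- Inputs: 1300 patients and 40 clinicians, so m = 1300/40 = 32.5 per clinician; shift d = 0.2 SD.
- Design effect = 1 + (m − 1) × ICC = 1 + 31.5 × 0.008 = 1.252.
- SE = √(1.252 × 4/1300) = 0.062.
- Two-sided 20% critical value = 1.282; d/SE = 0.2/0.062 = 3.22.
- Probability of selection ≈ Φ(3.22 − 1.28) ≈ 0.97.
- With ICC 0.05: design effect 2.575, SE 0.089, probability ≈ 0.83.
- With d = 0.1: 0.63 at ICC 0.008 and 0.45 at ICC 0.05.

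So if the score were put through the screen, a modest effect of the visit would often be enough to select it. This shows what the mislabeling could allow, not what the plan prescribes.

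**The case against.** The strongest reply concerns the control role. The covariate rule is limited to baseline variables. The control-variable block of Table 2 also contains TLFB and other measures at follow-up, and a CRAFFT tick in a column that footnote a limits to intervention-arm patients. Such values cannot all be meant as covariates, so the heading groups measures by topic and is not an adjustment list. This stands. What is left of the control role is a label that does not match the rule.

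A reader might go further and infer that the primary HED estimate will be over-adjusted. For example, if 10–30% of a relative risk of 0.80 ran through connectedness, adjustment would give exp(0.9 × ln 0.80) = 0.82 to exp(0.7 × ln 0.80) = 0.86. The document does not support this. It plans no such adjustment under a literal reading, the mediated share appears nowhere in it, and the calculation only restates the share assumed.

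It is also fair to say that connectedness is not among the hypothesized mediators, that the counseling lasts 5 to 10 minutes, and that the scale's items are not shown. It is therefore not established that the intervention raises the score. This limits the claim to a possible effect but does not rescue the moderator role, because the design provides no previsit value that would be safe to use.

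Finally, moderation is exploratory and its details may be settled in an analysis plan. That limits the importance of the point. However, an analysis plan can drop the score from the role but cannot recover a previsit measurement that was never taken.

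**Conclusion.** The point holds for the exploratory moderator analysis. Connectedness is given a moderator role but is measured only after a visit that includes rapport building. Because arm may affect the score, its interaction with arm would not describe effect modification by a baseline characteristic. The interaction would be interpretable in that way only if the visit left the score unaffected by arm, which the document neither states nor lets one check.

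For the control role, the fault is a mismatch between the Table 2 heading and the baseline-only covariate rule. No bias in the primary or secondary effect estimates is shown. Neither the size nor the direction of any distortion can be derived from the document, which gives no effect of the visit on connectedness and no association between connectedness and HED.

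**What to change.** - Remove the postvisit connectedness score from the moderator list and from the control-variable block of Table 2. Treat it as a process measure or a possible mediator. Number of prior visits can stay in both places. This is a change of wording and costs nothing in data collection.
- If moderation by connectedness is wanted, add the scale to the existing previsit survey for all remaining enrolments, and use only that value as moderator or covariate. The Results section expects recruitment to run until late 2024 or early 2025; once enrolment has closed, only the first step is available.

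The second step costs one more scale in a survey of about 20 minutes. The moderator analysis would cover only participants enrolled after the change, with less precision. Patients new to the clinician may be unable to rate connectedness before the visit, so their handling would need to be stated in advance.

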#### Data Collection

##### Clinicians

Enrolled clinicians are assigned a unique numeric identifier for use in data collection throughout the study. A baseline survey assesses previous experience and training and UC practices around screening, brief intervention, and referral to treatment (10 min), as well as training on study procedures and human subjects protections (up to 90 min; all clinicians). Clinicians assigned to the intervention arm additionally complete brief (5 min each) postsession evaluation surveys after each live training session and a final summative evaluation after all training components have concluded. Clinician surveys and evaluations are completed on paper or by email or SMS text message link to an online survey per clinician preference. After adolescent recruitment and intervention delivery have concluded at a practice, intervention clinicians complete a 10-minute debriefing survey assessing experience using the CRAFFT-IS and seeking suggestions for improving the system, as well as participate in a 30- to 60-minute interview or focus group (along with participating staff) to offer feedback on their study experience.

##### Adolescents

All adolescent participants are assigned a unique numeric identifier at the time of recruitment for use in data collection, storage, and linkage throughout their study participation. Once assented, participants indicate their contact preferences. Adolescents who agree to have their data shared with the NIAAA_DA_ are assigned a Global Unique Identifier using their first, middle, and last names; sex assigned at birth; and date and city of birth. Global Unique Identifiers are numeric codes that allow participant data to be submitted to the NIAAA_DA_ without any personally identifiable information. All participants self-administer the confidential electronic previsit survey (approximately 20 min; refer to Table 2 for details on all surveys), and participants seeing an intervention clinician complete the screening and psychoeducational components of the CRAFFT-IS (5 min) before seeing their clinician. After their visit, all participants complete the immediate postvisit survey (approximately 10 min), and then, through the 12-month follow-up period, brief monthly surveys about their past 30-day substance use and longer surveys at 3, 6, 9, and 12 months (approximately 15 min each). Participants may choose to skip questions or entire surveys and still remain in the study.

All surveys can be completed electronically on smartphones and desktop or tablet computers through a link sent by SMS text message or email to participants’ personal mobile phone numbers or email addresses, as preferred. Electronic surveys are protected by a password set by the adolescent. Adolescents can also complete a survey by mobile phone with a study RA. If the adolescent does not complete a survey after electronic reminders, a study RA will call the adolescent to encourage survey completion.

